### Randomization

The trial biostatistician will set up the centralized randomization using an SSL secured, password-protected web-based technology. Site will be the only stratification factor for administrative reasons. At the time of the recruitment dialogue, the research assistants will be unaware of the arm to which a participant would be assigned. Following signed consent, verbal confirmation of eligibility, and completion of baseline measures, the research assistant will log onto the randomization website, enter each participant’s code number, and will receive the random group assignment. Based upon the assignment, the research assistant will direct the participant to the room where their first intervention session will take place without revealing their assignment to them. Great care will be taken to ensure that agreement to participate and selection of the intervention schedule will be obtained prior to random assignment so that participation could not be affected by the recruiter’s or participant’s knowledge of assignment.

### Interventions

#### Control condition: University-provided brochures

To match the current ‘standard of care’ at Canadian universities, participants will be invited to take and read brochures on sexual assault selected from those available on their Canadian university campus. It is not possible to provide identical brochures across all three sites as each contains city-specific community services and sexual assault hotlines. However, the content of the brochures regarding sexual assault are similar and all sites’ brochures include general information on sexual assault and ‘date-rape’ drugs and post-rape legal and medical advice. One of two research assistants at each site will conduct each session, asking the participants to take brochures they are interested in, read them over, and ask any questions they may have. Questions will be answered in a group setting or individually if a participant stays after other participants have left to ask their question privately. Interaction between participants and the research assistant on the topic will be limited to 10–15 minutes after all preliminary activities (e.g., settling, getting food or beverages) are completed and will be audio recorded for verification.

#### Intervention condition: Enhanced AAA Sexual Assault Resistance program

The program consists of four separate units which use a combination of information-providing games, mini-lectures, facilitated discussion, brainstorming, large and small group activities, application and practice with DVD and audio clips, written scenarios, and role plays [57]. Participants will have a choice of either 1 unit per week over 4 weeks or all 4 units in one weekend (2 each day). At the first session, which will immediately follow the baseline session and randomization, participants will receive a resource kit including brochures and other resources. All sessions will be audio recorded.

##### **Unit 1**(3 hours)

The ‘Assess’ component focuses on improving assessment of risk for sexual assault in situations involving male acquaintances and developing problem-solving strategies to reduce risk. Personal relevance is heightened through the use of local statistics and a physical demonstration of the probability of sexual assault for women in the room. Sexual assault definitions and laws are presented briefly. ‘Assess’ is also related to the part of the process where the woman has communicated that she does not wish to engage in a sexual act and the man ignores her wishes and “continue[s] to touch, bully, or threaten” [41], p. 299. Beginning in Assess and developed further in later units, women are trained to identify this situation as dangerous and to take into account aspects of the situation such as isolation, possible escape routes, etc. Considerable time is spent providing women with empirically-based information on environmental/situational cues (e.g., alcohol) and men’s behaviour danger/risk cues [58], connecting these to gender and dating stereotypes, and giving women practice identifying increased risk and coming up with non-restrictive ways around it (i.e., ways to reduce the potential perpetrator’s advantage while still enjoying social situations).

##### **Unit 2**(3 hours)

The ‘Acknowledge’ component assists women to recognize more quickly the inherent danger in situations that have turned coercive and to explore ways to overcome emotional barriers which can prevent women from engaging in forceful resistance against known men. “Reluctance to label the situation as rape slows her protective response” [41], p. 299 and most women who are assaulted do not label their experience as rape [59]. In this unit, women’s personal sexual rights are reinforced. Exercises facilitate the exploration of the sometimes competing goals in social situations such as the desire for romantic (or friend) relationships and the need for personal safety [60]. The facilitators debunk the miscommunication hypothesis i.e., the argument that women are not clear enough in their sexual refusals or do not mean “no” when they say “no;” [61,62], and provide practice for women to emotionally prepare for and respond to common verbal coercion strategies [63].

##### **Unit 3**(3 hours)

The ‘Act’ component presents a range of potential options for resistance depending on elements of the situation, the man’s actions, and the success of early strategies. Typical self-defence strategies are often rejected by women because they are reluctant to use tactics such as “keys in the eye” against a man they have been dating or know socially. In fact, the strategies that women are most likely to use in acquaintance rape situations are precisely those that men say they are most likely to ignore [64] and which are least effective [45,65,66]. There is a brief discussion of the myths that undermine women’s resistance (e.g., the unsupported claim that women who defend themselves are hurt worse) [67]. Research evidence on the ineffectiveness of certain tactics and the effectiveness of forceful verbal and physical resistance are provided [45,68-70]. Each woman is encouraged to create a ‘tool box’ of forceful strategies that she would be willing to employ against a man she knows who is threatening her sexual integrity, and to escalate her resistance if any early strategies she tries are ineffective. Physical self-defence training (based on WenDo) includes standard instruction in making a fist, yelling in a way that fuels self-defence efforts, assessing vulnerable parts of the body, as well as techniques for punching and kicking. Additional strategies focus on defending against men in more common acquaintance situations (e.g., breaking wrist or choke holds, getting out from under someone using body weight to restrain you). This component also includes discussion of the need to overcome the emotional barriers to forceful physical defence against male acquaintances when the threat demands it.

##### **Unit 4**(3 hours)

This unit adapts content from *The Our Whole Lives* (OWL) sexuality education curriculum [56] and takes what women have learned from the previous three units and applies them in a more focused way to longer term romantic and sexual relationships. The unit is designed to assist participants to become more comfortable talking about sexuality, to expand discussions of sexual practices beyond intercourse, facilitate identification of women’s own sexual values and desires, sexual boundaries, and safety needs, and provide practice in communicating this knowledge in an assertive and self-efficacious manner, as well as increase women’s overall understanding of what healthy sexual relationships mean to them. This ensures that the education program is more fully integrated into participants’ lives.

### Assessments

At baseline, participants will complete computerized surveys prior to being randomized. They will then go immediately to their first intervention session, either to receive their brochures or to attend their first educational unit. To assess knowledge acquisition, intervention participants will have their 1st follow-up assessment 1 week after the last intervention session with control participants matched to the same interval. Subsequent follow-up assessments will occur at 6, 12, 18, and 24 months from the date of randomization. We will measure outcomes using in-person computerized surveys at baseline and 1 week after the last intervention session. All other follow-ups will use secure web-based surveys linked only by participant codes to protect privacy.

### Outcome measures

#### Primary

Completed sexual assault (rape) will have occurred when a participant indicates she has had at least one experience of sexual intercourse (oral, anal, or vaginal) that was threatened, forced, or drugged (completed, not attempted) in the period between the previous outcome measurement and the present; answered ‘once’ or more to any of 9 questions (involving oral sex, vaginal penetration, and/or anal penetration “without consent” when the woman was “too drunk or out of it to stop what was happening”, was threatened with physical harm to herself or others she cares about, and/or was forced, “for example holding me down with their body weight, pinning my arms, or having a weapon”) on the *Sexual Experiences Survey* - *Short Form Victimization* SES-SFV, [71]. Month of occurrence will be recorded to permit time-to-event analyses. Previous versions of the SES have been used in large university, college, and community samples, and it is considered the gold standard. Responses on the scale are stable across administrations. Test-retest reliability is very high, and responses are also comparable to those received through interviewing women [72]. Concurrent validity has been demonstrated using correlations between sexual victimization as measured with the SES and variables predicted to be affected or influenced by that victimization, for example, hostility toward men [73,74]. Construct validity has been demonstrated when women’s descriptions of sexual experiences were rated by interviewers (on the items of the SES) and compared to the women’s own responses on the SES [75].

#### Secondary

The expanded cognitive appraisal model upon which the educational program is built outlines the process through which changes to the primary outcome are accomplished. Outcomes corresponding to secondary hypotheses (a) through (d) measure these intermediary processes. The outcome corresponding to the secondary hypothesis (e) measures attitudes likely to be affected by the program and is related to successful coping with sexual assaults. These will allow targeted revision to the program if necessary.

(a) Perception of risk of sexual assault by male acquaintances will be measured by a single item, “What are your chances of being raped by someone you know?” which has been adapted from Gray, et al. [76].

(b) Belief that women can defend themselves if a sexual assault situation were to arise (*Self-defense self-efficacy*: Marx et al.’s [77] adaptation of Ozer and Bandura [78] – higher scores indicate greater self-efficacy). This is a 7-item instrument with responses ranging from “not at all confident” to “very confident” on a 7-point scale. The instrument has a 0.83 Cronbach’s alpha level of internal consistency. Two items were also added to specifically measure a participant’s sense of her own ability to defend herself against unwanted sexual experiences, “How successful do you believe you would be in fighting off or otherwise stopping an attempted rape by a stranger?” and “How successful do you believe you would be in fighting off or otherwise stopping an attempted rape by a man you know (e.g., a man you are dating)?” Participants answer each of these two questions on a 7-point scale, ranging from *completely successful* to *completely unsuccessful*. These questions were pilot tested and found to have a 0.87 Cronbach’s alpha level of internal consistency.

(c) Knowledge of effective rape resistance strategies will be measured by identification of a greater number of forceful physical and forceful verbal strategies in response to threatening hypothetical situations (*Resistance measure*, [79]) and real situations (items requesting details following sexual assaults experienced, questions added to SES items, [48]). Testa et al.’s [79] measure follows a scenario depicting an interaction where the participant is on a date with “an attractive man” (p. 666). These items about the participant’s “intended behaviour” break down into 3 subscales: direct-resistance, polite-resistance, and passive-response. The direct-resistance subscale, which is our focus, has high internal consistency ranging from 0.89 to 0.94 and validity demonstrated by the authors. Additional, added questions, “If a man I knew (e.g., a date) tried to force me to have sex with him when I didn’t want to, I would …”, If a stranger tried to force me to have sex with him when I didn’t want to, I would …” were pilot tested to ensure clarity and consistency of coding of responses. Scoring is based on Ullman’s [45] study of the tactics used by women who avoided completed rape and has high inter-rater reliability (Cohen’s kappa > 0.90).

(d) Ability to realistically assess risk of harm in hypothetical scenarios where acquaintance sexual assault is likely will be measured using the: (1) *Risk perception* questionnaire [79]. Using the same scenario with “an attractive man” as the strategies measure above, the risk perception measure presents statements of 10 possible outcomes, 4 positive and 6 negative. The participants answer on a 7-point scale, from *not at all* to *very likely*, what they perceive the outcome of the interaction will be. Internal consistency is in excess of 0.85 by Cronbach’s alpha; (2) *Risk Perception Survey* (RPS) [80]. Two vignettes, one based on a stranger and one on an acquaintance situation “were designed to incorporate risk factors identified in the literature and included … clear risk factors and ambiguous risk factors” (p. 162). Participants are asked to identify the line number at which they feel uncomfortable (identify risk) and the point at which they would leave (take action). Higher scores indicate toleration of higher risk in the situation. These are the only measures available and once completed cannot be used again due to familiarity with the scenarios. As such, this outcome can only be measured 3 times (Testa’s once; Messman-Moore’s twice, once each for the stranger and acquaintance versions). The timing of measuring this outcome is spread out across the first year of follow-up.

(e) Beliefs and attitudes about rape will be measured by endorsement of rape myths (*Illinois Rape Myth Acceptance Scale* IRMA-SF,[81], and misinformation about the causes of rape (*Perceived Causes of Rape Scale* PCOR,[82,83]. The IRMA has the best psychometric properties of any rape myth scale, having excellent criterion-related validity (correlations with measures of sexism and hostility toward women) and reliability. Internal consistency is high (Cronbach’s alpha > 0.82). The PCOR “provides [an] assessment of a range of people’s beliefs about the causes of rape that are not exclusively rape myths” [83], p. 228. This 32-item instrument provides participants with the stem “Rape is caused by ....” and they answer how much they agree with a list of causes. Our focus is on the *Female Precipitation* subscale which has the best internal consistency. Test-retest reliability of 0.87 is also good.

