### Statistical analyses

Analyses will be performed after all women have completed their one-year follow-up and at the end of the trial. Following the intention-to-treat principle, a participant will be included in the analysis if she is randomized. Using SAS software [92] the primary (and tertiary) analyses will compare the proportion of women with completed sexual assaults between groups using a Wald test from a log-binomial regression model (PROC GENMOD) that adjusts for compound symmetry (CS) clustering using generalized estimating equations. Covariates will be added to the model if differences among baseline characteristics are observed. In addition, a test for interaction will be performed using the above model to assess whether there is a differential treatment effect depending upon whether the women participated in the weekend versus weekday programs. Women who are lost to follow-up or drop out can affect the validity of the group comparison if (a) sexual assault is related to being lost or dropped and (b) it is differential between groups. Thus, baseline characteristics of women who are lost and drop out will be compared to women who complete the trial. In addition, the missing data mechanism will be formally tested [93] to determine whether it is Missing Completely at Random (MCAR) or is Missing at Random (MAR). Freedom from completed sexual assault will be compared between groups using Cox regression (PROC PHREG) with a robust sandwich covariance matrix to account for the clustering. Women who are lost to follow-up or drop out will have their data censored at the time of last contact.

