For the secondary outcomes which are all continuous (or at least ordinal) longitudinal, repeated measures analysis of covariance (ANCOVA) will be used to compare intervention arms across the follow-up periods, adjusting for baseline scores on the instruments. Generalized linear models (PROC MIXED) will be used to correctly adjust the variance estimates for CS clustering. Recognizing that some of the instruments have ordinal responses, a rank-based ANCOVA will also be performed to assess congruency with the parametric analyses. For completeness in assessing the effect of missingness, two additional analyses will be conducted: (a) a ‘per-protocol’ analysis among participants who attend all sessions and respond to the 1-year SES-SFV questions; (b) multiple imputation of five data sets (PROC MI and MIANALYZE) using a discriminant function for binary outcomes and Markov chain Monte Carlo for continuous outcomes, assuming the missing data mechanism is MAR. The literature, for example [49], suggests that prior sexual assault can be a modifier with respect to the effectiveness of sexual assault resistance programs. Accordingly, program effects will be compared for women with and without sexual assault histories at baseline.

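### The real-assault part of secondary outcome (c) can be scored only in women who report an event after randomisation, so an arm comparison on it is not a randomised one

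*Protocol article*

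**What the plan says.** Under Outcome measures, Secondary, outcome (c) has two sources. The first is "identification of a greater number of forceful physical and forceful verbal strategies in response to threatening hypothetical situations": a scenario-based resistance measure, of which the direct-resistance subscale is named as the focus, plus two added open-ended questions (a man she knows, a stranger). The second is "real situations (items requesting details following sexual assaults experienced, questions added to SES items". Scoring rests on a study of "the tactics used by women who avoided completed rape".

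Under Statistical analyses, the secondary outcomes are described as all continuous or at least ordinal, and longitudinal, and they share one method: "repeated measures analysis of covariance (ANCOVA) will be used to compare intervention arms across the follow-up periods, adjusting for baseline scores on the instruments". For the analysis set, the same section says that "a participant will be included in the analysis if she is randomized". Nothing there treats the real-situation items differently.

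On use, the introduction to the secondary outcomes says: "These will allow targeted revision to the program if necessary".

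**The concern.** A woman with no reported event has no real-situation score. This is not a missing answer: the quantity does not exist for her. The women who do have a score are defined by something that happens after randomisation and that the program is designed to alter. Comparing arms within that group gives up the balance that randomisation provides, and adjusting for baseline scores does not restore it.

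The selection is tied to the behaviour being scored. Unit 3 teaches forceful resistance as effective, and the scoring is built on tactics of women who avoided completed rape. A tactic that works can therefore remove a woman from the scored group, or move her to a milder category within it. The primary outcome also counts assaults on women "too drunk or out of it to stop what was happening", where the scope for forceful resistance is different, so a change in the mix of circumstances would change the average score even if no woman's resistance changed.

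At stake is the reading of one mechanism outcome. A difference or a null on these items could be credited to, or held against, the resistance content when it reflects who ended up in the group.

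**Working it through.** **1. The plan's own figures.** Inputs from Sample size considerations: 25% v 17.5%, two-sided 5%, 80% power. The pooled-variance formula for two proportions without continuity correction gives 466 per arm, 932 in total, as stated. Design effect: 1 + (20 − 1) × 0.02 = 1.38. Total: 932 × 1.38 ÷ 0.75 = 1714.9, against 1716 stated, which is close enough. That is 1716 ÷ 2 = 858 per arm. The document gives no figure for outcome (c).

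**2. Who could supply a real-situation score.** With 10% loss at one year, 858 × 0.9 = 772 per arm. If the items followed completed assaults only:
- control: 772 × 0.25 = 193
- program: 772 × 0.175 = 135

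So the group would be a quarter or less of each arm, and its membership differs by arm under the trial's own hypothesis.

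**3. Can the direction of bias be fixed?** The documents give no split of assaults by circumstance, so the inputs here are assumed, and they serve only to test the sign. Let control assaults be 12.5% forced or threatened and 12.5% incapacitated (sum 25%). Let 60% of women in the forced or threatened group resist forcefully, in both arms, and none in the incapacitated group. There is then no true change in resistance. The share of assaulted women reporting forceful resistance is 0.6 × forced ÷ total.

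| Assumed program arm | Forced + incapacitated | Control | Program |
|---|---|---|---|
| Mostly forced assaults prevented | 6.25% + 11.25% = 17.5% | 0.6 × 12.5 ÷ 25 = 30.0% | 0.6 × 6.25 ÷ 17.5 = 21.4% |
| Mostly incapacitated assaults prevented | 11.25% + 6.25% = 17.5% | 30.0% | 0.6 × 11.25 ÷ 17.5 = 38.6% |

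Both rows meet the planned 25% v 17.5%, and they give opposite spurious differences. The second row cannot be excluded: Unit 1 covers alcohol among the situational risk cues.

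**4. Can the size be fixed?** Use a second assumed model. A share p of attacked women resists forcefully, with p = 0.30 in control, and forceful resistance multiplies the risk of completion by r. The program raises p until completed assault falls by the planned 30%:
- p(program) = [1 − 0.7 × (0.3r + 0.7)] ÷ (1 − r)
- share among assaulted women = pr ÷ (pr + 1 − p)

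| r | True share, control v program | Share among assaulted |
|---|---|---|
| 0 | 30% v 51% | 0% v 0% |
| 0.1 | 30% v 54% | 4.1% v 10.6% |
| 0.5 | 30% v 81% | 17.6% v 68.1% |

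The distortion runs from total (r = 0) to almost none (r = 0.5: +51 points true, +50 observed). The documents do not give r.

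**5. Baseline adjustment.** If a real-situation score is also taken at baseline and used as the covariate, it exists only for women with an event before enrolment. The adjusted model would then use only women with events both before and after. The article does not say that the detail items are asked at baseline, so this step is conditional.

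**6. Imputation.** The planned multiple imputation under MAR does not solve this, because a woman with no event has no unobserved value to fill in.

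**The case against.** The best reply is that no sentence says the arms will be compared among assaulted women only. The ANCOVA sentence is generic, and an article may leave to the analysis plan whether the detail items form a score, are combined with the scenario measure or are tabulated. That tempers the point but does not remove it. The article makes these items part of how (c) is measured, assigns one between-arm method to all secondary outcomes, and describes those outcomes in terms that do not fit this component.

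Second, the answering group may be wider than completed rape: the SES-SFV also records forced contact and coercion, as the Tertiary outcomes show. This stands. A woman who stopped an assault short of completion may still answer, which would weaken the selection. Women with no reportable event would still be outside the group.

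Third, program revision would draw on outcomes (a) to (e) together, and (c) has hypothetical measures open to every participant. This also stands: the sponsor need not be misled by one component.

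A reader might infer more: that the bias must run against the program, so that an effective program would appear to have taught nothing. The documents do not support that. The sign depends on which assaults are prevented, and the size on how effective resistance is; neither is given.

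**Conclusion.** The point holds as a limited one. Followed as written, the plan tests the real-situation component of (c) between groups selected after randomisation by what the program is meant to change. The result can be biased either way, by an amount the documents do not determine. The figures in steps 3 and 4 of the check show only that neither sign nor size is fixed; they are not estimates of the bias. The counts of 193 and 135 rest on the planning rates and on the assumption that only completed assaults trigger the items.

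The conclusion rests on reading the outcome definition and the analysis sentence together. It does not touch the primary outcome, the other secondary outcomes or the hypothetical-situation part of (c). Nor does it follow that the real-situation items are useless for program development; read descriptively, with the selection stated, they may still inform it.

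**What to change.** In the definition of outcome (c) and in Statistical analyses, state that hypothesis (c) is tested only on the hypothetical-situation measures (the direct-resistance subscale and the two open-ended questions) in all randomised women. State that the real-situation items are reported descriptively, by arm and tactic, with no between-arm test, and that the women answering them are selected after randomisation.

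A composite defined for everyone, such as assault without forceful resistance, is not a substitute test of (c), because it falls whenever incidence falls. In the first row of the step 3 table, where resistance does not change, it would be 25% − 7.5% = 17.5% in control and 17.5% − 3.75% = 13.75% in the program arm.

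The cost is wording only: no new data are needed, and one component of (c) becomes descriptive.
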